|  |                                                                                                                  | 
Brain: The brain and cognitive impairment measured using a battery of cognitive tests at start of study (t=0) and at 6-monthly intervals up to 48 months.
 
Immune System: Immonocompetency determined by altered immune cell repertoires and effector function assessed using blood sampling at regular (6 month) intervals using various experimental protocols.
 
Eye: Structural changes including retinal nerve fibre layer thinning assessed by retinal scanning (OCT) at the start, mid-point and end of the study.
 
Metabolism: Metabolism and metabolic health assessed using faecal and blood samples obtained at regular (6-12 month) intervals.
 
Identifying change in virus (DNA/RNA), archaea and fungal populations from faecal samples obtained at regular intervals (6 months) throughout the study.
 |
|  | 
3: To determine if changes in the gut microbiota detected over time equally affect its different members?
 |                                                                                                                                                                                                                                                                                                                                                                                                                                                                                                                                                                                                                                                                                                                                                                                                                                                    |

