## 8 Phase 1 - Screening and Recruitment Phase

### 8.1 Telephone Contact

Once a reply sheet from a participant from Stream 1 (Annex 8.1) or Stream 2 (Annex 8.2) is received, they will receive an initial telephone call from the QIB Researcher. If a reply sheet is received from a participant from Stream 3 (Annex 8.3), they will receive the initial telephone call from a NSFT Research Nurse. Each participant will receive an overview of the study requirements and any questions will be answered. The Study Researcher will use the Telephone Contact section of the Telephone Contact/Pre-Study Visit Checklist (Annex 9) as a guide to providing all study information and checking eligibility before making the Pre-Study Visit appointment. It is anticipated that the Telephone Contact call will last approximately 20 minutes. If the participant is unsure of their medical history, they can check this with their GP and let the Study Researcher/NSFT Research team know before the Pre-Study Visit appointment is made.

If the participant has received antibiotics within 14 days, or a vaccination within 28 days of the planned Pre-Study Visit, the Pre-Study Visit will be delayed for the

appropriate washout period (antibiotics is 14 days from the date of the last dose and 28 days from the date of the last vaccination). This will ensure a baseline consistency at the point of consenting at the Pre-Study Visit. Any other circumstances which may delay the Pre-Study Visit from being booked will be discussed on an individual basis.

If the participant is not eligible to participate, they will be given the reason why and thanked for their time and interest in the study.

If the participant is eligible and is happy with the study requirements, the Pre-Study Visit appointment will be made.

For Stream 1 & 2, participants will attend the QI CRF. For Stream 3 participants, they will be seen in their own home by the NSFT Research Nurse as it is acknowledged that they would feel more comfortable. During the Telephone Contact discussion, the participant will be made aware that the Pre-Study Visit will last up to 2.5 hours and that during this time, the Study Researcher/NSFT Research Nurse will do the following: -

- ✚ Go through all elements of the study in full detail.
- ✚ Go through the Participant Instructions for Stool Collection (Annex 13) and the Participant Stool Sample Collection Log (Annex 14).

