## 8.2 Pre-Study Visit.

It is acknowledged that the Pre-Study Visit is a lengthy process (up to 2.5 hours) so the Study Researcher will schedule in regular comfort breaks that are convenient for the participant. The Study Researcher will follow the structure of this visit as described above.

The Study researcher will go through the consent form with the participant and encourage any questions they may have at this stage; after which the participant will sign the consent form agreeing to participate in the study.

After completing the Informed Consent process (see Sections 11.1), a copy of the completed Study Consent and Biorepository Consent (if applicable) (see section 11.2) will be given to the participant. Copies of all completed consent forms will be posted to the participant if the participant is from Stream 3.

Following completion of the Cognitive Test (mini-ACE) and the associated questionnaire (CCI), the participant will be provided with their Baseline Visit stool collection pack. See Section 11.3.1 for a full description of the Cognitive tests and associated questionnaires. It will be explained to the participant that within 5-10 working days, the anonymised Cognitive Tests will be scored by [name] or an experienced Research Assistant within his team, or a member of the Study Research Team to ascertain whether the participant is within the required threshold to be included in the study (see Section 11.3.1 for scoring thresholds).

The participant will then be contacted by the QIB Study Researcher to confirm their final eligibility, by telephone by prior arrangement. If their score does not fall within the required threshold, they will be thanked for their time and interest in the study

(Section 16). If the participant feels worried or anxious because they have any concerns, the Study Researcher will act sensitively and reassure the participant that the tests are for research purposes and are not indicative of any clinical diagnosis. Copies of the completed tests will be routinely sent to their GP (Annex 25) if the participant wishes to discuss them.

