## 9 Phase 2 - Sample and Data Collection Phase

Participants will be sent a standard reminder (by their preferred method) about their next Study Visit within one week in advance of their appointment (Annex 33).

They will also be reminded to bring a list of all their current prescribed and over-the-counter medication. The participant will be asked to let the Study Researcher know if they are taking or have taken antibiotics within one week of their scheduled appointment. In this case, the appointment will need to be rescheduled as a two-week washout is required from when the last dose of antibiotics was taken. In addition, they will also be reminded to let us know of any travel or flu vaccinations scheduled within 28 days of their appointment as a 28-day washout is required. The participant can record these on their Study Appointment Schedule (Annex 19). At the start of each study visit, the participant will be asked if they are still happy to continue with the study.

All study-related travel and car parking costs to QI CRF, NNUH and Beccles Hospital will be reimbursed to the participant at the end of each study visit. Mileage will be reimbursed at the current QIB standard rate of 45p/mile. Taxi and bus fares will be reimbursed on production of a valid receipt. Light refreshments and comfort breaks will be offered.

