## 9.1 Study Visits

### 9.1.1 Baseline Visit (approximately up to 3 weeks from Pre-Study Visit).

The participant will be provided with their Study Appointment Schedule (Annex 19) and a Study Identification carry card (Annex 20). The Study Researcher will go through these with the participant. The participant will also receive a freezer magnet displaying the study logo. This will act as a reminder for the participant to freeze their ice-packs ahead of stool sample collection. Participants will be informed that they will be sent a one-page newsletter either via an online link (Annex 38) or provided as a hard copy at the appropriate study visit to provide recruitment updates, study reminders and sign post participants to related information of interest.

This visit will take approximately 2 hours. Participants will be required to attend the QI CRF for their Baseline Visit for the following: -

[figure not shown] Undergo Cognitive tests and associated Questionnaires (see Section 11.3.1 for full description): -

- ❖ Mini ACE – repeated again at this visit for reliability
- ❖ CCI – repeated again at this visit for reliability

- ❖ PHQ 9 (Patient Health Questionnaire)
- ❖ Supermarket Test
- ❖ Sea Hero Test
- ❖ CBI-R (participant)
- ❖ RCFT (Rey Complex Figure Test)
- ❖ TMT (Trail Making Test)
- ❖ BPQ (Body Perception Questionnaire)

The CCI, PHQ9, CBI-R and BPQ are self-administered tests. The remainder activities are delivered by the Study Researcher.

- ✚ Complete the Full Health Questionnaire.
- ✚ Obtain Blood sample – 40 ml (8 teaspoons).
- ✚ Collect physical measurements (height, Tanita scales measurement, BP and hand grip strength measurements).
- ✚ Discuss the OCT/OCT (A) scan and brain MRI scan (as appropriate) appointment as below. Participants will be made aware that they would need to allow up to 1.5hrs for the brain MRI and up to 3 hours for the OCT/OCT (A) scan.

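### The vaccination prompt at the sampling visits (Section 9) is narrower than the washout rule at the Pre-Study Visit (Section 8.1), so some blood samples inside the protocol's own 28 days can reach the immune outcomes

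*Protocol*

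**What the plan says.** Two places in the protocol deal with vaccination before a visit.

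Section 8.1 concerns the Pre-Study Visit. The trigger is "If the participant has received antibiotics within 14 days, or a vaccination within 28 days of the planned Pre-Study Visit", and the visit is then put back until 28 days after the last vaccination. No vaccine type is named. The reason given is: "This will ensure a baseline consistency at the point of consenting at the Pre-Study Visit". According to Section 8.2 and the Schedule of Events, that visit consists of consent, the mini-ACE, the CCI and the issue of the stool pack: "Following completion of the Cognitive Test (mini-ACE) and the associated questionnaire (CCI), the participant will be provided with their Baseline Visit stool collection pack". No blood is drawn and no stool is handed in.

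Section 9 concerns Baseline and Study Visits 1 to 8, where all scheduled blood and stool samples are collected. Its opening sentence sets the timing: "Participants will be sent a standard reminder (by their preferred method) about their next Study Visit within one week in advance of their appointment". On vaccination, "they will also be reminded to let us know of any travel or flu vaccinations scheduled within 28 days of their appointment", and the justification follows at once: "as a 28-day washout is required".

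The Synopsis lists an immune outcome under the second secondary objective, with immunocompetency judged from "altered immune cell repertoires and effector function assessed using blood sampling". Sections 13.1.3 and 13.1.3.1 add activated immune cells, cytokines, immunoglobulins and antibodies.

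**The concern.** The prompt in Section 9 does not match the washout it is meant to enforce. It is narrower than Section 8.1 in two respects: which vaccines count (travel or flu, against any) and whether those already given count (scheduled, against received). The narrower wording sits at the visits where samples are taken, and the broader wording at the one visit where none are.

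A participant who had some other vaccine ten days before a sampling visit has nothing to report under Section 9 and would attend as planned. Blood drawn inside the interval that the protocol itself calls for could then be used for immune outcomes, with no stated means of telling it apart. Visits would also be handled differently according to vaccine type, for no reason that the protocol gives.

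**Working it through.** The plan states no figure on this point, so there is none to reproduce. The check is a comparison of the two rules, followed by arithmetic in days.

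**1. The two rules side by side**

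| | Section 8.1 | Section 9 |
|---|---|---|
| Visits covered | Pre-Study Visit | Baseline, Study Visits 1–8 |
| Vaccines named | any | travel or flu |
| Status | received | scheduled |
| Interval | 28 days | 28 days |
| Stated action | visit delayed | participant reports; rescheduling is spelled out for antibiotics but not for vaccination |
| Blood or stool taken | neither | both |

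**2. What the reminder can catch.** It is sent at most 7 days before the appointment. By then at least 28 − 7 = 21 of the 28 days have passed, which is 21/28 = 75% of the window. A vaccination in that stretch has already been given, so on the plain wording it is no longer scheduled. This applies to travel and flu vaccines as well.

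**3. What Section 8.1 does for Baseline.** Baseline follows the Pre-Study Visit by up to about 3 weeks (Section 9.1.1), or 21 days. Section 8.1 therefore clears at least the earliest 28 − 21 = 7 of the 28 days before the first samples, and more if Baseline comes sooner. A vaccination on the day after the Pre-Study Visit would be at most 21 − 1 = 20 days old at Baseline, which is at least 8 days short of 28. The protection is partial.

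**4. Other text that might close the gap.** At the start of each visit, Section 9 has the participant asked only about willingness to continue. The Partial Health Questionnaire (Section 15.2.2) covers health status, medication and marked changes in routine. It does not name vaccination, and no rescheduling follows from it.

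**5. Possible size.** Inputs from the protocol: 360 participants, 48 months of follow-up (1,461 days), 8 follow-up visits, of which 4 (Visits 2, 4, 6, 8) include the serum and plasma draw (Section 11.5). Assumptions, not in the protocol: vaccinations fall evenly over follow-up, and 10 to 50% of participants have one vaccination that the prompt misses.

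- Assumed vaccinations: 0.10 × 360 = 36 to 0.50 × 360 = 180.
- Share falling within 28 days before any follow-up visit: 8 × 28 / 1,461 = 224/1,461 = 15.3%.
- Visits affected: 36 × 0.153 = 5.5 to 180 × 0.153 = 27.6, so about 6 to 28 of 8 × 360 = 2,880, or 0.2 to 1.0%.
- Share falling within 28 days before a serum/plasma draw: 4 × 28 / 1,461 = 112/1,461 = 7.7%.
- Draws affected: 36 × 0.077 = 2.8 to 180 × 0.077 = 13.8, so about 3 to 14 of 4 × 360 = 1,440, or 0.2 to 1.0%.

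The serum/plasma count bears more closely on immune function, because Visits 1, 3, 5 and 7 draw only full blood count, biochemistry and troponin. Both counts ignore attrition, which Section 19.2 puts at roughly 20% over four years, and both leave out Baseline.

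**The case against.** The strongest reply is that Section 9 contains a reminder, not the rule. Its closing clause, "as a 28-day washout is required", names no vaccine type and no direction in time. Travel and flu vaccines may simply be those a participant is most likely to plan, and *scheduled* may have been meant loosely. The forms that would settle this are not shown: the reminder (Annex 33), the appointment schedule (Annex 19), the case report form (Annex 18) and the Partial Health Questionnaire (Annex 16.2). Participants also bring a medication list, and consent covers access to GP and hospital notes, so recent vaccinations might be traced later.

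Part of this stands. The annexes may be broader, and later tracing is possible. But if the clause does state a general washout, the written prompt still fails to enforce it, and nothing visible in the protocol asks about other vaccines or acts on them.

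A reader might also infer more than the text supports:

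- *That recently vaccinated participants do enter the data.* The protocol gives no vaccination rate. It supports only that they can.
- *That the microbiota data are compromised.* Nothing in the protocol says that vaccination alters stool microbiota, and the primary outcome is bacterial composition.
- *That the broader rule protects no sample at all.* Step 3 shows that it partly protects Baseline.
- *That the protocol declares such samples unfit.* It does not. Its stated reason in Section 8.1 is consistency at consent.

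**Conclusion.** The point holds as a minor inconsistency. Sections 8.1 and 9 disagree on which vaccinations count and on whether those already given count, and the narrower wording applies where samples are taken. Followed as written, it lets some participants inside the protocol's own 28-day interval contribute blood to immune outcomes, which are one part of a secondary objective.

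The number cannot be known from the protocol. The range of 0.2 to 1.0% rests wholly on the assumed 10 to 50% uptake and on vaccinations spread evenly over time; clustering near visits, or more than one missed vaccination per participant, would change it. The planned 360 participants and the power table are unaffected.

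**What to change.** Reconcile Sections 8.1 and 9, and Annex 33 if it repeats the narrower wording, so that the prompt uses the same definition of vaccination and the same look-back as the washout it enforces. Which rule applies is for the sponsor to decide; the request is only that the passages agree.

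Record vaccination type and date at each sampling visit, so that immune analyses can be repeated without samples taken inside the washout.

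The cost is a change of wording and one entry on the visit form. If the sponsor settles on the broader reading, a few more visits will be rescheduled. At Study Visits 1 to 8 the one-month window either side should generally absorb this. A full 28-day delay after a vaccination between the Pre-Study Visit and Baseline would exceed the approximate 21 days allowed, so the sponsor should say how that case is handled.

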## 9.1 Study Visits

### 9.1.1 Baseline Visit (approximately up to 3 weeks from Pre-Study Visit).

The participant will be provided with their Study Appointment Schedule (Annex 19) and a Study Identification carry card (Annex 20). The Study Researcher will go through these with the participant. The participant will also receive a freezer magnet displaying the study logo. This will act as a reminder for the participant to freeze their ice-packs ahead of stool sample collection. Participants will be informed that they will be sent a one-page newsletter either via an online link (Annex 38) or provided as a hard copy at the appropriate study visit to provide recruitment updates, study reminders and sign post participants to related information of interest.

This visit will take approximately 2 hours. Participants will be required to attend the QI CRF for their Baseline Visit for the following: -

[figure not shown] Undergo Cognitive tests and associated Questionnaires (see Section 11.3.1 for full description): -

- ❖ Mini ACE – repeated again at this visit for reliability
- ❖ CCI – repeated again at this visit for reliability

- ❖ PHQ 9 (Patient Health Questionnaire)
- ❖ Supermarket Test
- ❖ Sea Hero Test
- ❖ CBI-R (participant)
- ❖ RCFT (Rey Complex Figure Test)
- ❖ TMT (Trail Making Test)
- ❖ BPQ (Body Perception Questionnaire)

The CCI, PHQ9, CBI-R and BPQ are self-administered tests. The remainder activities are delivered by the Study Researcher.

- ✚ Complete the Full Health Questionnaire.
- ✚ Obtain Blood sample – 40 ml (8 teaspoons).
- ✚ Collect physical measurements (height, Tanita scales measurement, BP and hand grip strength measurements).
- ✚ Discuss the OCT/OCT (A) scan and brain MRI scan (as appropriate) appointment as below. Participants will be made aware that they would need to allow up to 1.5hrs for the brain MRI and up to 3 hours for the OCT/OCT (A) scan.

#### 9.1.1.1 Baseline brain MRI scan appointment

The Baseline Visit brain MRI scan appointment will be scheduled within 6 weeks of the Baseline Visit, and the appointment letter (Annex 24) will be sent by the Study Researcher along with the NHS MRI Safety Questionnaire (Annex 17). The participant will also receive a reminder (by their preferred method) from the Study Researcher within one week of when the appointment is due (Annex 35).

The MRI appointment/follow-up process flow is shown in Figure 6.

[figure not shown]

#### 9.1.1.2 Baseline OCT/OCT (A) scan appointment

The Baseline OCT/OCT (A) Scan appointment at Beccles Hospital will be scheduled for within one month of the Baseline Visit. The appointment letter (Annex 22) will be sent from Beccles Hospital and will routinely request participants to bring in a copy of their current prescriptions. This letter will be sent with an OCT/OCT (A) Patient Information Sheet (Annex 23) generated by Beccles Hospital.

The participant will also receive a reminder (by their preferred method) from the Study Researcher within one week of when the appointment is due (Annex 34).

The OCT/OCT (A) appointment and follow-up process flow is shown in Figure 7.

[figure not shown]

### 9.1.2 Study Visits 1, 3, 5 & 7

Study Visit 1 will be 6 months from the Baseline Visit.

Study Visit 3 will be 18 months from the Baseline Visit.

Study Visit 5 will be 30 months from the Baseline Visit.

Study Visit 7 will be 42 months from the Baseline Visit.

These visits will take approximately 2 hours. Participants will be required to attend the QI CRF for the following at each visit: -

- + Drop off the cool box containing their stool sample.
- + Pick up any replacement stool collection items ahead of next Study Visit.
- + Blood sample – 15 ml (3 teaspoons).
- + Complete the Partial Health Questionnaire.
- + Undergo Cognitive tests and associated questionnaires: -
  - ❖ Mini ACE
  - ❖ CCI
  - ❖ PHQ 9 (Patient Health Questionnaire)
  - ❖ Supermarket Test
  - ❖ Sea Hero Test
  - ❖ CBI-R (participant)
  - ❖ RCFT (Rey Complex Figure Test)
  - ❖ TMT (Trail Making Test)
  - ❖ BPQ (Body Perception Questionnaire)

The Study Researcher will explain the following at the end of each of the following Study Visits:-

- ❖ Study Visit 3 - remind the participant that they will receive an appointment letter from Beccles Hospital for their OCT scan, which will be scheduled to take place within one month before or one month after Study Visit 4.
- ❖ Study Visit 7 - remind participant that they will receive an appointment letter from Beccles Hospital for their OCT (A) scan. This appointment will be scheduled for around 4 weeks before Study visit 8 and will take place at Beccles Hospital. If applicable, the Study Researcher will go through the MRI checklist and remind participant that they will receive an appointment letter for a MRI scan at NNUH around 6 weeks before Study Visit 8. Both scans will be scheduled prior to Study Visit 8 where possible so that the participant can be reimbursed for any travel and parking costs at Study Visit 8 (final visit).

### 9.1.3 Study Visits 2, 4, 6 & 8

Study Visit 2 will be 12 months from the Baseline Visit.

Study Visit 4 will be 24 months from the Baseline Visit.

Study Visit 6 will be 36 months from the Baseline Visit.

Study Visit 8 will be 48 months from the Baseline Visit.

These visits will take approximately 45 mins. Participants will be required to attend QI CRF for the following at each visit: -

- + Drop off the cool box containing their stool sample.
- + Pick up any replacement stool collection items ahead of next Study Visit (apart from Study Visit 8).
- + Blood sample – 40 ml (8 teaspoons).
- + Physical measurement collection (height, Tanita Scales Measurement, BP and hand grip strength measurements).
- + Complete the Partial Health Questionnaire.

The Study Researcher will provide the following at the end of each of the following Study Visits:-

- ❖ Study Visit 4 - as a thank you for their participation so far, each participant will receive a Love2shop voucher to the value of £10.
- ❖ Study Visit 8 - the participant will be thanked for their participation in the study and given a further Love2shop voucher to the value of £15 for their time and any inconvenience.

